## Abstract

**Background:**

A left atrial posterior wall isolation (LAPWI) is one of the atrial fibrillation (AF) ablation strategies.

**Hypothesis:**

We hypothesized that an additional empirical LAPWI would increase the freedom from recurrent atrial arrhythmias as compared to standard AF ablation in persistent AF patients.

**Methods:**

The CORNERSTONE AF study is a prospective, randomized, multicenter study investigating patients with AF persisting for >7 days and <3 years undergoing first‐time AF ablation. They will be randomized to pulmonary vein isolation (PVI) or PVI + LAPWI in a 1:1 manner. Although PVI can be performed with either radiofrequency catheters or cryoballoons, only radiofrequency catheters will be permitted to achieve LAPWIs. Additional focal ablation targeting non‐pulmonary vein triggers will be allowed. A total of 516 patients will be enrolled in 17 centers between August 2022 and February 2024 based on the calculation with 80% power, considering the assumption that 65% and 75% of the PVI and PVI + LAPWI group patients will be free from atrial arrhythmia recurrence 18‐months postprocedure (10% of dropout). The primary endpoint is freedom from documented atrial arrhythmias 18 months postsingle procedures. Clinical follow‐up will include 7‐day ambulatory electrocardiograms and routine outpatient consultations by electrophysiologists at 1, 3, 6, 9, 12, and 18 months postprocedure.

**Results:**

As of August 2023, a total of 331 patients (68 ± 9 years, 270 men, 43 longstanding persistent AF) have been enrolled.

**Conclusions:**

The CORNERSTONE AF study is a prospective, randomized, multicenter trial designed to evaluate the efficacy and safety of an adjunctive empirical LAPWI following standard AF ablation in persistent AF patients.

## INTRODUCTION

1

Catheter ablation is an important therapeutic strategy for rhythm control of atrial fibrillation (AF) and its cornerstone is pulmonary vein isolation (PVI).^1^ In fact, although there are various approaches for treating AF, the STAR AF Ⅱ trial failed to prove any additional efficacy of linear ablation or complex fractionated electrograms ablation compared to a PVI alone.^2^ However, in persistent AF (PsAF) patients, a sufficient clinical outcome could not be obtained by a PVI alone, considering the result that 40% of patients were suffering from atrial arrhythmias recurrences after a single ablation procedure in STAR AF Ⅱ. One of the possible substrates beyond the pulmonary veins (PVs) is the left atrial posterior wall (LAPW). The LAPW is included in the PV component of the left atrium (LA) and its smooth tissue differs embryologically from the other primitive cardiac tube.^3^ The various distributions of the myocardial architecture can produce nonuniform anisotropic conduction leading to arrhythmogenicity.

The LAPW isolation (LAPWI), so called “box isolation,” is a strategy targeting the arrhythmogenicity of the PV component, which is achieved by linear ablation of the roof and floor of the LA connecting both PVI circles in addition to the PVI. Although a meta‐analysis including 11 studies showed a lower atrial arrhythmia recurrence rate after an adjunctive LAPWI as compared with a PVI alone in PsAF or longstanding PsAF (long‐PsAF) patients, the analysis included studies in which the recurrence rate was higher in the LAPWI group.^4^ Among the randomized controlled trials (RCTs) included in the meta‐analysis, two RCTs failed to prove any superiority of the LAPWI to a PVI alone.^4^, ^5^ Further, two RCTs favorable for an LAPWI in the meta‐analysis were not considered to be randomized studies for the aim of comparing PVI alone and an additional LAPWI.^6^, ^7^ The evidence of an empiric LAPWI in PsAF/long‐PsAF patients has not been established sufficiently yet.

On the other hand, triggers other than the PVs (non‐PV triggers), which initiate AF, have been focused on as a strategy for AF ablation. It has been reported that non‐PV triggers are identified in ~10% of PsAF/long‐PsAF patients.^8^ In another investigation, sufficient clinical outcomes could be obtained in those with treatable non‐PV triggers as compared with those with persistent triggers after ablation for non‐PV triggers such as including a superior vena cava (SVC) isolation or LAPWI.^9^ According to the expert consensus statement, it is recommended to consider ablation of reproducible focal triggers identified outside the PV ostia (Class Ⅱa), which is more strongly recommended than an LAPWI (Class Ⅱb).^10^ However, this ablation strategy was not adopted in most of the trials in which the efficacy of an additional LAPWI was examined. Therefore, there is a value in evaluating the true efficacy of an additional empirical LAPWI after a conceivable best practice of AF ablation including a non‐PV trigger ablation in addition to the PVI in PsAF/long‐PsAF patients.

With regard to the safety, possible gastroesophageal complications need to be considered, especially when an LAPWI is added because the PV component is closely adjacent to the esophagus and periesophageal vagal nerve branches. There are some investigations of esophageal thermal injury including cases in which linear ablation of the roof or floor of the LA was performed, but they showed that linear ablation was not associated with increasing esophageal injuries.^11^, ^12^ Some observational studies reported that the prevalence of gastric hypomotility detected on gastroesophageal endoscopy, which is attributed to the periesophageal vagal nerve injury, was significantly higher in cases with an additional LAPWI as compared to those with a PVI alone.^13^, ^14^ Further investigations regarding the safety after an additional LAPWI are required.

The incidence of iatrogenic atrial tachycardia (AT) after the procedure would be a potential disadvantage of an adjunctive LAPWI. According to the meta‐analysis of LAPWIs, the prevalence of an AT recurrence tends to be higher after an additional LAPWI than after a PVI alone.^4^ In addition, there has been a report that demonstrated that peri‐mitral ATs were the main cause of recurrent ATs^15^ after an LAPWI. The influence of an additional LAPWI should be investigated further.

We planned this prospective RCT of the CORNERSTONE AF study to prove the efficacy of an empiric LAPWI in addition to the standard AF ablation in PsAF/long‐PsAF patients. We hypothesized that an additional empirical LAPWI would increase the freedom from recurrent atrial arrhythmias as compared to standard AF ablation in PsAF/long‐PsAF patients. We also aim to investigate the details of the procedure with regard to not only the efficacy but also the safety including gastric hypomotility.

## METHODS

2

### Study design

2.1

The CORNERSTONE AF study is a prospective, multicenter, randomized, open‐label trial performed at 17 centers in Japan (coordinating center: Tokyo Medical and Dental University, principal investigator: [name], details in Supporting Information: Appendix), aiming to assess the efficacy of empirical LAPWI in addition to standard AF ablation in PsAF/long‐PsAF patients. AF is classified according to the latest guidelines.^1^ The patients with AF lasting for more than 7 days and less than 3 years, who undergo a de novo AF ablation, will be enrolled and centrally allocated to a PVI alone or PVI + LAPWI in a 1:1 manner before the ablation procedure using a permuted block randomization. The duration of AF will be defined as the persistence of the AF. Patients with paroxysmal AF will not be enrolled. Randomization will be stratified by the institution, type of AF (i.e., PsAF or long‐PsAF), and kind of instrument utilized for the PVI (i.e., radiofrequency catheter or cryoballoon) (Figure 1). The outcome of the randomization will not be blinded to either the operators, the patients or the attending physicians. No funding was used to support this work. This study has been registered at UMIN (University hospital Medical Information Network) Clinical Trials Registry (UMIN 000047638, https://center6.umin.ac.jp/cgi-open-bin/ctr_e/ctr_view.cgi?recptno=R000054321) and has been approved by the institutional review board at each participating hospital. A signed, institutional review board‐approved informed consent form will be obtained from each patient before enrollment.

**Figure 1 clc24164-fig-0001:**
[figure not shown]
Randomization details. For patients with persistent AF (PsAF), it will be allowed to perform the PVI by either a radiofrequency catheter or CB. Note that the operators should choose what they will use for the PVI before randomization. After the decision, randomization will be implemented before the procedure. Regarding longstanding PsAF (long‐PsAF), only a radiofrequency catheter will be permitted to be utilized for the PVI. Allocation of the patients to a PVI alone or a PVI + LAPWI will be performed in a 1:1 manner in each group, namely those with PsAF, who will undergo a PVI with a radiofrequency catheter; those with PsAF, who will undergo a PVI with a CB; and those with long‐PsAF (shown as red arrows). The large blue circles indicate CB ablation lesions and small red circles indicate radiofrequency ablation lesions. AF, atrial fibrillation; AFL, atrial flutter; AT, atrial tachycardia; CB, cryoballoon; LAPWI, left atrial posterior wall isolation; PVI, pulmonary vein isolation; RF, radiofrequency.

### Endpoints

2.2

The primary endpoint is designed as the freedom from atrial arrhythmia recurrence such as AF, AT, and atrial flutter (AFL) with or without antiarrhythmic drugs at 18 months after a single procedure. Atrial arrhythmia recurrence is defined as documented AF/AT/AFL lasting more than 30 s after a 90‐day blanking period according to the guidelines.^1^ The safety endpoints include the incidence of procedure‐related major complications such as a stroke, transient ischemic attack, PV stenosis, cardiac tamponade, pericarditis, phrenic nerve injury, major bleeding, vascular access complications (significant groin hematoma, pseudoaneurysm, arteriovenous fistula), atrioesophageal fistulae, gastric hypomotility, heart failure, myocardial infarction, and death according to the guidelines.^1^ To ensure the safety, all adverse events will be reported by the investigators to the coordinating center and reviewed by the institutional review board every month (the members are listed in the Supporting Information: Appendix). In addition, data monitoring will be performed every 6 months by two cardiologists independent of the present study.

The secondary endpoints include the freedom from individual components of the primary outcome (AF, AT, and AFL), atrial arrhythmia freedom after multiple procedures, atrial arrhythmia burden reduction, recurrent arrhythmia types (paroxysmal or persistent), symptomatic atrial arrhythmia recurrence free rate, comparison regarding the atrial arrhythmia freedoms between the radiofrequency group and cryoballoon group in PsAF patients, direct‐current cardioversion free rate, procedure time and fluoroscopy time, success rate of the LAPWI, dimension of the additional isolated area of the LAPW after the LAPWI, freedom from re‐do procedures, durability of the PVI and LAPWI during the second procedure among the patients who underwent a redo procedure, number of repeat procedures, and gastrointestinal symptoms during the periprocedural period. The predictors of atrial arrhythmia recurrence will be also examined among the various factors including the existence of low voltage areas and the kind of devices such as the three‐dimensional mapping systems and ablation catheters.

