### Limitations

4.1

There are several limitations to be mentioned. First, an additional focal ablation of non‐PV triggers will be permitted, therefore, we cannot compare the outcomes between a PVI alone and a PVI + LAPWI as in the CAPLA trial. However, we aim to evaluate the impact of an empirical LAPWI in addition to standard AF ablation, which consists of a PVI (Class Ⅰ indication) and non‐PV trigger ablation (Class Ⅱa indication). Second, the randomization will not be blinded to the patients and physicians during the follow‐up, or there will be no blinded committee to assess the endpoint, which might produce some bias, however, the results of 7‐day Holter ECG recordings will be analyzed by staff blinded to the randomization. Third, the PVI will be performed with either a cryoballoon or radiofrequency catheter, which will produce an additional variable. However, we aim to assess the impact of an additional LAPWI in the clinical practice. Considering that the cryoballoon is widely utilized for the PVI, even for PsAF, it is reasonable to include cryoballoon ablation. Fourth, there will be no committee that will oversee the efficacy and safety of the study. However, to ensure the safety, all adverse events will be reported to the coordinating center, and the institutional review board will assess whether there is any issue to continue the study every month (member list in Supporting Information: Appendix). In addition, data monitoring will be performed every 6 months by 2 cardiologists independent of this study (member list in Supporting Information: Appendix). Fifth, although the procedural endpoint has been clearly determined, the detailed ablation protocol to reach the endpoint is left to each operator.

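### The only named between-arm safety comparison counts stroke, heart failure, infarction and death as procedure-related complications, with no stated assessor or blinding of that judgement; an all-cause count by arm should sit beside it

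*Protocol article*

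**What the plan says.** Section 2.2 (Endpoints) introduces safety with "The safety endpoints include the incidence of procedure‐related major complications such as a stroke, transient ischemic attack, PV stenosis, cardiac tamponade". The same list closes with "gastric hypomotility, heart failure, myocardial infarction, and death according to the guidelines", so the procedure-related qualifier covers those events too, and their definitions are referred to the guidelines. The secondary endpoints in that section contain no outcome for death, stroke, infarction or heart failure of any cause. For safety, Section 2.7 (Statistical analysis) names a comparison of the complication rate between the groups and nothing else.

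On blinding, Section 2.1 says: "The outcome of the randomization will not be blinded to either the operators, the patients or the attending physicians". Section 4.1 (Limitations) adds that "there will be no blinded committee to assess the endpoint, which might produce some bias", and that "there will be no committee that will oversee the efficacy and safety of the study".

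On collection and review, Section 2.2 says that "all adverse events will be reported by the investigators to the coordinating center and reviewed by the institutional review board every month", and that "data monitoring will be performed every 6 months by two cardiologists independent of the present study". Section 2.5 schedules visits up to 18 months. Section 5 gives safety, alongside efficacy, as something the trial is designed to evaluate.

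**The concern.** For tamponade, groin hematoma or phrenic nerve injury, relatedness is close to self-evident and the qualifier costs little. A stroke, a heart failure event, an infarction or a death some months after ablation is different. There, relatedness is a judgement, and it decides whether the event enters the stated comparison between arms.

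Nothing in the article shows that this judgement is protected from knowledge of the arm. If it leans differently in the two arms, events move into or out of the comparison for reasons unrelated to treatment, and the lean could go either way. Later events may also fall outside the comparison altogether. At stake is the credibility of the safety half of the trial's stated aim. The primary efficacy result is not affected.

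**Working it through.** The point concerns a definition, and the plan has no safety figure to reproduce. The first check is therefore textual.

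1. **Does the qualifier reach death, stroke, infarction and heart failure?** Yes. They stand in the same list in Section 2.2.
2. **Does another stated endpoint catch them whatever the cause?** No. None is among the secondary endpoints, and Section 2.7 names only the complication rate.
3. **Who decides relatedness, within what window, and blinded or not?** The article does not say. Investigators report events, the review board reviews them monthly, and two independent cardiologists monitor data every 6 months. None of these is described as judging attribution or as blinded. The blinded reading in Section 4.1 covers the 7-day Holter recordings only.
4. **Are unfiltered data collected?** Section 2.2 says that all adverse events go to the coordinating center. The article gives no end date for that reporting. Taking it to run to the 18-month visit is an assumption.

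**Illustration of sensitivity.** The event risks and attribution shares are assumptions. The arm size is 516 / 2 = 258, from Section 2.6, before any dropout.

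Expected attributed events = 258 × true risk × share attributed.
Observed ratio (LAPWI : PVI) = true ratio × (LAPWI share / PVI share).

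| True risk, PVI vs LAPWI | Share attributed, PVI / LAPWI | Events, PVI vs LAPWI | Ratio |
|---|---|---|---|
| 3% vs 5% | 100% / 100% | 7.7 vs 12.9 | 1.67 |
| 3% vs 5% | 100% / 80% | 7.7 vs 10.3 | 1.33 |
| 3% vs 5% | 100% / 60% | 7.7 vs 7.7 | 1.00 |
| 2% vs 4% | 100% / 100% | 5.2 vs 10.3 | 2.00 |
| 2% vs 4% | 100% / 80% | 5.2 vs 8.3 | 1.60 |
| 2% vs 4% | 100% / 60% | 5.2 vs 6.2 | 1.20 |
| 2% vs 2% | 80% / 100% | 4.1 vs 5.2 | 1.25 |
| 2% vs 2% | 60% / 100% | 3.1 vs 5.2 | 1.67 |

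Rows 2, 3, 5 and 6 show a true excess shrinking or disappearing. The last two show an apparent excess where none exists. In every case the shift comes from about one to five events.

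**What the all-cause comparison could detect.** For 2% versus 4% with 258 per arm, the standard error is √[(0.02 × 0.98 + 0.04 × 0.96) / 258] = 0.0150. The standardized difference is 0.02 / 0.0150 ≈ 1.33. Two-sided 5% power is about Φ(1.33 − 1.96) ≈ 0.27. The added table is therefore descriptive and cannot serve as a test.

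**The case against.** The strongest case against is that the text is looser than the point needs. The endpoint sentence uses open, illustrative wording, so it does not exclude other safety analyses. It also refers definitions to the guidelines, which may set time windows or criteria that leave a site little discretion. Adverse event tables by arm are ordinary content of a full protocol or analysis plan, and procedure-related complications are a legitimate endpoint for a procedural trial.

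Much of this stands, and it rules out four stronger readings that a reader might infer:

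- **That these events count only if attributed to the procedure.** The wording is not exhaustive. What can be said is that no other comparison is named.
- **That unblinded investigators make the call.** No assessor is named. The review board and the independent cardiologists also see data, although neither is described as adjudicating. The remark in Section 4.1 about having no blinded committee is answered there by blinded Holter reading, so it most naturally concerns the arrhythmia endpoint.
- **That late embolic or heart failure harm from LAPWI is expected.** The article gives no such mechanism. The Introduction raises gastroesophageal injury and iatrogenic atrial tachycardia. These have a symptom questionnaire and an AT recurrence-free rate, neither of which needs a relatedness judgement.
- **That the endpoint would conceal a large excess.** Any such size depends on assumed risks and attribution shares.

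The objection does not remove the point. The relatedness restriction is something the article states, so the point does not rest on detail missing from a condensed text. A guideline time window, if there is one, would reduce discretion but could leave later events outside the comparison even more firmly.

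**Conclusion.** The point holds in limited form. As stated, the between-arm comparison of stroke/TIA, heart failure, infarction and death passes through an attribution step that has no named assessor and no stated blinding, in an open-label trial. It is open to bias in either direction and may omit later events. The documents do not show that such bias will occur or how large it would be. The table of shifts shows only that, at assumed risks of 2% to 5%, a handful of attribution decisions can change the impression given. Sample size, power and the primary endpoint are untouched. This is an inexpensive improvement to the safety reporting and does not threaten the trial's main conclusion.

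**What to change.** Add to Section 2.2, with a matching line in Section 2.7, a descriptive comparison by randomized arm of all-cause death, stroke/TIA, myocardial infarction and heart failure events, from the index procedure to 18 months and regardless of attribution. Take the events from the adverse event reports already sent to the coordinating center, and confirm that this reporting runs to 18 months. Keep the procedure-related complication rate beside it, labelled as attributed without stated blinding. If blinded attribution is in fact planned, say so and name the assessor's role.

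The cost is one or two sentences and one table, with no change to sample size and, if reporting already runs to 18 months, no new visits or data collection. Unrelated background events will add noise, and with few events the comparison has low power, so it should be presented as descriptive only.

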### Study patients

2.3

All criteria for inclusion and exclusion are presented in Table 1. All patients must exhibit an episode of continuous AF that is sustained >7 days in the year before the procedure. Exclusion criteria will be as follows: (1) patients with AF lasting >3 years; (2) patients aged <20 years old; (3) patients with a history of previous cardiac surgery; (4) patients with an LA diameter of >55 mm measured in the parasternal view on trans‐thoracic echocardiography; (5) patients with heart failure with a New York Heart Association class Ⅳ; (6) patients with hemodialysis; and (7) patients presumed to require the use of amiodarone after the procedure such as those with ventricular tachycardia. The other criteria are described in Table 1. Patients with a history of a previous cavotricuspid isthmus ablation or paroxysmal supraventricular tachycardia ablation will not be excluded.

**Table 1 clc24164-tbl-0001:** Criteria for inclusion and exclusion.

Inclusion
Patients with PsAF (lasting >7 days)
Patients undergoing a de novo AF ablation
Patients expected to fulfill an 18‐month follow‐up after the procedure
Exclusion
Patients with AF lasting >3 years
Patients aged <20‐year‐old
Patients with a history of previous cardiac surgery
Patients with an LAD > 55 mm
Patients with heart failure with NYHA class Ⅳ
Patients with a reversible cause such as hyperthyroidism
Patients with contraindications to anticoagulants
Patients with intracardiac thrombi
Pregnant patients
Patients with hemodialysis
Patients presumed to require the use of amiodarone after the procedure

Abbreviations: AF, atrial fibrillation; LAD, left atrial diameter; PsAF, persistent AF; NYHA, New York Heart Association.

### Ablation procedure

2.4

The details of the ablation procedure such as the vascular approach, anesthesia method, use of an esophageal temperature probe, or choice of the 3‐dimensional mapping system will be left to each institution's discretion. Uninterrupted oral anticoagulants will be generally required. First, a PVI will be performed utilizing either a radiofrequency catheter or cryoballoon in PsAF patients and will be performed with a radiofrequency catheter in long‐PsAF patients. In the PsAF patients, the choice of radiofrequency catheter or cryoballoon will be determined before the randomization (Figure 1). This is because cryoballoon use has been approved for a PVI alone in PsAF patients but not in long‐PsAF patients in Japan. All the ablation procedures can be performed during any rhythm (AF, sinus rhythm, and so on). After the confirmation of the electrical PVI, a voltage map of the LA will be created during sinus rhythm or atrial pacing rhythm, if sinus rhythm can be maintained. In the patients randomized to the LAPWI group, linear ablation of the LA roof and floor will be performed with a radiofrequency catheter (Figure 2). The endpoint of the LAPWI is defined as no near‐field potentials and no atrial capture when pacing is performed from inside the “box” with the ablation catheter with more than 5 V and a 2 ms output. If an LAPWI is not achieved after the LA roof and floor linear ablation, additional focal ablation of the LA posterior wall (inside the “box”) will be allowed. After the accomplishment of the LAPWI, a voltage map of the LA will be created again to assess the additional isolated area. In addition to the PVI or LAPWI, a cavotricuspid isthmus ablation and SVC isolation will not be prohibited. When non‐PV foci, which is defined as ones cause AF initiation or frequent atrial ectopy, will be identified by an isoproterenol infusion and/or electrical cardioversion, focal ablation will also be permitted. However, no other empirical ablation including linear ablation (mitral isthmus ablation, and so on), low voltage area ablation, electrogram based ablation, or vein of Marshall ethanol infusion will be allowed. In the patients randomized to the PVI group, an LAPWI will be considered only when the multiple triggers identified on the LAPW cannot be controlled by focal ablation. Otherwise, an LAPWI will not be permitted.

